## **MATERIALS & METHODS:**

**Trial design {8}:** It will be a parallel group, quadruple blind-randomized controlled pilot trial annexed with a laboratory based study.

**Study settings & duration {9}:** The clinical trial will be carried out at the Aga Khan University Hospital (AKUH), Karachi, Pakistan. The total duration of the study is expected to be 6 months i.e. August 2020-January 2021. The viral PCR tests will be done at main AKUH clinical laboratories whereas the immunological tests (cytokine analysis) will be done at the Juma research laboratory of AKUH. The study protocol is already registered at [www.clinicaltrials.gov](http://www.clinicaltrials.gov) with ID# NCT 04341688.

**Sampling technique & Eligibility criteria {10}:** Non probability, purposive sampling technique will be followed to identify a total of 50 participants for this study. The inclusion criteria are laboratory confirmed COVID-19 positive males or females (in the age range of 18-65 years), with mild to moderate disease, already admitted in the AKUH. Subjects who have more than 7 days of the onset of COVID-19 symptoms, edentulous patients, subjects with low Glasgow coma score, intubated patients, history of radiotherapy or chemotherapy will be excluded. Patients who are being treated with any form of oral or parenteral antiviral therapy will be excluded. Patients with known pre-existing chronic mucosal lesions such as lichen planus will also be excluded. Patients who are allergic to the study drugs (Povidone-Iodine, Hydrogen Peroxide, Neem Extract or Hypertonic Saline) will also be excluded.

**Intervention {11a}:** Group A (n=10) patients on 10 ml gargle and nasal lavage using 0.2% Povidone-Iodine (Betadiene® by Aviro Health Inc./ Pyodine® by Brooks Pharma Inc.) for 20-30 seconds, thrice daily for 6 days. Group B (n=10) patients will be subjected to 10 ml gargle and nasal lavage using 1% Hydrogen peroxide (HP® by Karachi Chemicals Products Inc./ ActiveOxy® by Boumatic Inc.) for 20-30 seconds, thrice daily for 6 days. Group C will comprised of (n=10) subjects on 10ml gargle and nasal lavage using Neem extract solution (*Azardirachta indica*)

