formulated by Karachi University (chemistry department laboratories) for 20-30 seconds, thrice daily for 6 days. Group D (n=10) patients will use 2% hypertonic saline (Plabottle® by Otsuka Inc.) gargle and nasal lavage for a similar time period. Group E (n=10) will serve as positive controls. These will be given simple distilled water gargles and nasal lavage for 20-30 seconds, thrice daily for six days. For nasal lavage, a special douche syringe will be provided to each participant. Its use will be thoroughly explained by the data collection officer. After each use, patient is not supposed to eat, drink or mouth rinse for next 30 minutes.

**Discontinuation of intervention {11b}:** Patients who develop rashes, or any other mucosal reaction in oral mucosa or patients who do not wish to continue with the gargles and nasal lavage will be discontinued in the study.

**Compliance on intervention {11c}:** The data collection officer will monitor the amount of gargling solution consumed on daily basis to record the patient compliance on intervention. And once the study is over, the residual bottle will be collected and sent to the incineration. Similarly, any unused/ partially used study drug bottle will be destroyed via incineration.

**Concomitant care {11d}:** Study participants will continue to get their needed routine inpatient medical/pulmonology care concomitantly as per the individual requirements under the care of the attending physician(s).

**Outcomes {12}:** Primary outcome is the reduction in the intra-oral viral load confirmed with real time PCR. Secondary outcome is the change in inflammatory biomarkers (IL-2, IL-4, IL-6, IL-10, TNF- $\alpha$ , IFN- $\gamma$  and IL-17) profiles in the five study groups.

**Participants' timeline {13}:** The timeline has been added as a flow diagram at the end of the protocol. Please see figure 1 on page no. 15.

**Sample Size {14}:** As there is no prior work on this research question, so no assumptions for the sample size calculation could be made. The present study will serve as a pilot trial. We intend to study 50 patients in five study groups. For details, please refer to figure 1 on page no. 15.

**Recruitment {15}:** Patients who are laboratory confirmed COVID-19 within 7 days of the onset of their symptoms who are already admitted as inpatient at the Aga Khan University Hospital, Karachi, Pakistan will be contacted for a voluntarily participation in the study.

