**Retention of study participants {18b}:** To retain maximum number of patients in the study, the data collection officer will keep the contact number of all the recruited patients, so that even if they are discharged from the hospital, they will be encouraged to continue with the study protocol and present to us on the day 7 at the AKUH dedicated COVID-19 testing facility for the collection of their endpoint pharyngeal swabs.

**Data management {19}:** A trained data collection officer will be responsible for data entry, coding, security, and storage. To ensure data quality, double data entry will be followed. The data collection officer will ensure coordination with the investigators and the statistician.

The period of retention of the data will be according to the CTU policy on this subject i.e. 15 years after the completion of the trial. The biological samples (pharyngeal swabs), and the partially consumed study drug will be discarded via incineration immediately after the data collection.

**Data Analysis {20}:** Data will be analyzed using SPSS for Windows (version 23.0 SPSS) and Graph Pad Prism 7.0 software.

Mean and standard deviation of the continuous variables (age, COVID-19 viral counts and cytokine profiles at baseline and endpoint etc.) will be computed. Frequency distribution of the categorical variables will be determined (gender, co-morbidities, presence of hypertension, diabetes, periodontal status etc.) Repeated measures ANOVA will be used to compare the reduction in intra-oral viral load and the changes in the inflammatory biomarkers in the study groups. In case of substantially low count of participants in the study groups, non-parametric tests such as Kruskal-Wallis or Friedman test will be employed. Generalized Estimation Equation (GEE) will be done to predict changes in the COVID-19 viral load and cytokine profiles. A subset analysis using Zero inflated negative binomial (ZINB) model will be employed, provided a

significant reduction in viral load is observed in any of the study groups. A p-value of  $<0.05$  will be taken as statistically significant. {20a}

The **biases and confounders** can be taken care at following four levels:

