At recruitment stage, we will use restriction i.e. only those COVID-19 positive subjects will be recruited who have no other major co-morbidities. At intervention assignment, the random group allocation will ensure even distribution of the confounders in the study groups, thus their differential effect on the outcome will be taken care of. At analysis stage, we will employ GEE regression analysis (as described above) to account for biases and confounders and lastly, the subset analysis will stratify the data and nullify the effect of biases.

Interim analysis {20b} is not planned on account of a short duration of the study. Intention to treat analysis (ITT) will be adopted for missing data and protocol violations or deviations by uncompliant patients. {20c}

**Data monitoring {21a}:** It will be done bimonthly at two levels. The data monitoring committee comprising of principal and co-investigators will be responsible for the monitoring the data at the primary level whereas the CTU at the university level will oversee and monitor the overall conduct of the study.

The decision of termination of the study {21b} will be made in consultation with the director CTU and the sponsors/ funding agency. The decision will be made after mutual consensus of the parties.

**Harms/ adverse reaction reporting {22}:** The adverse events will be documented for each patient and will be reported bimonthly to the clinical trial unit (CTU). This will also documented in the final report. Sponsor/ funders will be notified of the adverse event using their case report. Due to topical nature of the intervention, most likely harm would be an allergic reaction to any of the study drugs [Povidone-Iodine, Hydrogen Peroxide or Neem Extract (*Azadirachta indica*)]. In case of any serious harm, the advice of the primary attending physician will take precedence over others. However, such patient will be discontinued in the trial, CTU and sponsors informed and un-blinding will be followed as prescribed in section 17b. The role of patient's medical insurance will be decided on individual basis

**Study Audit {23}:** CTU reserves the right of carrying out study audit by internal or external auditors anytime.

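### The protocol says its subset analysis will nullify bias, but that analysis runs only after a significant viral-load fall and cannot have that property

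*Protocol*

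**What the plan says.** Protocol, Data Analysis {20}, describes the treatment comparison (repeated measures ANOVA, or a rank-based alternative if numbers are low) and a GEE. It then adds one further analysis, a subset analysis with a zero-inflated negative binomial model, on the condition that a "significant reduction in viral load is observed in any of the study groups". The significance level is 0.05. No stratifying variable is named for this analysis.

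The paragraph on biases and confounders that follows announces four levels of control: restriction at recruitment, random allocation, GEE at the analysis stage, and the subset analysis. On the third it says "At analysis stage, we will employ GEE regression analysis (as described above) to account for biases and confounders". On the fourth it says "lastly, the subset analysis will stratify the data and nullify the effect of biases".

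Arm size is fixed in Intervention {11a}, for example "Group A (n=10) patients on 10 ml gargle and nasal lavage using 0.2% Povidone-Iodine", with the same number in Groups B to E. Sample Size {14} says "We intend to study 50 patients in five study groups" and explains that there is no prior work, "so no assumptions for the sample size calculation could be made".

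**The concern.** Two statements in the protocol do not fit together. One presents the subset analysis as a protection against bias. The other makes its use depend on a significant finding. A safeguard against bias has to be in place whichever way the result falls. One that is switched on by a significant result does nothing when there is no such result, and when it does run, the data have already been selected for a favourable finding.

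The claimed effect is also too strong in itself. Stratification deals only with the factor used to form the strata. It does not touch biases that arise after randomisation. The protocol recognises two sources of these: discharged patients have to return for the day-7 swab (Retention {18b}), and a participant may recognise the solution (Un-blinding {17b}).

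At stake is how a subset result would be read. If the protocol says that this analysis nullifies bias, a reader of the final report could give it more weight than an imprecise, result-triggered analysis deserves.

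**Working it through.** **Plan's own figure.** 5 arms × 10 patients = 50, which agrees with Sample Size {14}. The protocol gives no effect size, standard deviation or power, so the main argument is textual. The figures below are illustrations, and their assumptions are stated.

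**1. The two passages side by side.** Data Analysis {20a}: the subset analysis is run if and only if a significant reduction is seen in some group. Biases paragraph: the subset analysis nullifies bias. If no group shows a significant reduction, the fourth level does not operate. If one does, the finding came first and the safeguard second.

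**2. How the trigger behaves.** The wording covers any study group, so on its face it includes Group E (distilled water). Assume that each arm is tested separately for change from baseline, two-sided at 0.05, independently.
- No true change in any arm: 1 − 0.95^5 = 22.6% chance of at least one significant change; counting falls only, 1 − 0.975^5 = 11.9%.
- Assumed natural fall of 0.5 SD of the paired change in every arm, water included (normal approximation): per arm Φ(0.5 × √10 − 1.96) = 0.352; any of five, 1 − (1 − 0.352)^5 ≈ 89%.
- Assumed natural fall of 1.0 SD: per arm 0.885; any of five, about 100%.

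On this reading the trigger does not separate a treatment effect from natural decline. If the trigger is instead a between-group test, these figures do not apply, but step 1 still does.

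**3. What stratifying can do in arms of 10.** An even split gives 10/2 = 5 per cell. For a binary factor with assumed prevalence p, the number of patients with the factor in an arm is Binomial(10, p).

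| p | some arm has fewer than 2 with the factor: 1 − (1 − P(X ≤ 1))^5 | some arm has none: 1 − (1 − (1 − p)^10)^5 |
|---|---|---|
| 15% | 98% | 67% |
| 25% | 75% | 25% |
| 35% | 36% | 7% |
| 50% | 5% | 0.5% |

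At 50% either side can be the smaller stratum. Counting both sides gives 1 − (1 − 22/1024)^5 = 10% and 1 − (1 − 2/1024)^5 = 1.0%.

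**4. Precision depends on use.** For a two-arm difference with an ideal 5/5 split, the standard error within one stratum is √(10/5) = 1.41 times the whole-arm value. If the two strata are pooled, it is 1.41/√2 = 1.0 times that value, so nothing is lost.

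**5. Multiplicity depends on use.** If each stratum is tested separately, one binary factor with one contrast gives 1 − 0.95^2 = 9.8%. Four active-versus-control contrasts in two levels give 8 tests and 1 − 0.95^8 = 34%, if independent. With pooling there is one test per contrast and this inflation does not arise.

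**6. Bias outside the stratifier.** In 20,000 simulated two-arm comparisons (10 per arm, no true effect, an assumed bias of 0.5 SD not caused by the stratifying factor), the mean estimate was 0.50 SD before stratification and 0.50 SD after it.

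**The case against.** The strongest reply is that this is one overstated clause about a conditional analysis that comes last in the list. Randomisation, restriction and an unconditional GEE already deal with confounding, and the trial is called a pilot. Much of this stands, and it rules out several stronger readings that a reader might infer.

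- *That a null result would receive no confounder control.* It would: the GEE is not tied to any result.
- *That stratification can remove no bias at all.* Stratifying on a measured prognostic factor can reduce chance imbalance in that factor.
- *That subset results would become the headline answer, or that claims would be made from single cells.* The protocol places the comparison in the ANOVA or its rank-based alternative, with the GEE, and gives the subset analysis no precedence.
- *That the trial carries a 9.8% or 34% false-positive rate, or a 1.41-fold loss of precision.* These hold only if each stratum is tested on its own. The protocol does not say so, and stratification for confounder control usually pools across strata.
- *That the missing exploratory label is itself a fault.* Subset definitions and labels are commonly left to a statistical analysis plan, which is not at hand.

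What the reply does not answer is the affirmative statement. No later detail about strata or models can make a result-triggered stratification of arms of 10 nullify bias.

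**Conclusion.** The concern holds in limited form. The protocol credits the subset analysis with a property that it cannot have: it starts only after a significant viral-load reduction, and stratifying corrects at most imbalance in the stratifying factor. This conclusion rests on the protocol's text and needs none of the assumed figures. The cell-size, trigger and error-rate calculations depend on assumed prevalences, natural decline, number of factors, independence and, for the error rates, separate testing by stratum. They show the scale of the difficulty and are not properties of the plan. No primary comparison, endpoint or sample size is affected. Severity: minor.

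**What to change.** In the biases and confounders paragraph, delete the closing clause on the subset analysis and change the announced number of levels from four to three.

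Take analysis-stage adjustment from a model on all randomised patients, run whatever the result, with day-7 viral load as outcome and baseline viral load as covariate. Both swabs are already scheduled in Specimen collection {18a}. This is a modelling choice as well as a wording change, so it should be stated consistently with the GEE in {20a}.

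Describe any subset or zero-inflated negative binomial result as exploratory, reported as estimates with 95% confidence intervals and without any claim that it corrects bias.

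The cost is a few sentences, with no extra patients, samples or assays. The sponsor gives up presenting subset results as bias-corrected.

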#### **Safety and effectiveness of the Neem leaf extract (*Azardirachta indica*) {34}:**

There is a substantial evidence on the effectiveness and safety of the Neem extract. Clinical trials have shown that Neem based mouthwashes are effective against chronic gingivitis (17,18) plaque retention (18, 19) and dental caries (20). The antiviral activity of Neem leaf (*Azardirachta indica*) has been established (21) especially herpes simplex virus type-1 (22), group B coxsackie viruses (23) and Novel H1N1 Flu virus. (24)

Regarding extraction process of Neem, (17) it will be done at the Chemistry department laboratories at the University of Karachi, Pakistan. Neem leaves will be dried under controlled condition, then its 20.0 g dry powder will be mixed with 100 ml of 70% (w/v) ethanol for a week in a round bottom flask with occasional shaking. This will be kept in the dark container to avoid effect of light. The extract will then be filtered through filter paper, measured and kept in an airtight container. The final mouthwash formulation to have 25% of Neem extract, 20.0% of Saccharin and Peppermint oil (<0.1%) as flavor. HPLC based analysis will ensure the quality control of the solution. (25)

#### **Why this study is important and why are we doing it?**

Pakistan is a resource restraint country, it's not possible to carry out coronavirus testing at mass scale. Simple, cost effective intervention against the present pandemic is highly desirable.

This research is important as there is no definitive management for Covid patients. At present, only preventive strategies such as frequent hand washing, use of mask, social distancing and avoidance of congregation is being followed. We have suggested a RCT to determine

effectiveness of simple mouthwash and nasal lavage (with antiviral agents) as a prophylaxis against viral colonization.

If we are able to demonstrate effectiveness of topical anti-viral mouthwash and nasal lavage then not only dentists, other clinicians involved in aerosol generating procedures (ENT, maxillofacial and anesthesiologists) could be benefited by simply doing a pre-procedure mouthwash and nasal lavage as a prophylaxis before embarking upon an aerosol generating procedure. Moreover, such Gargles based prophylaxis can be part of the routine management of patients visiting outpatient clinics where the status of Covid-19 is not known.

The risk of morbidity and mortality is high among physicians and nurses involved in the screening and management of Covid-19 patients. Globally, over 230 physicians and surgeons have died while taking care of these patients. The cause of death was high exposure of viral load. The antiviral gargles and nasal lavage can decrease the fatalities among doctors and nurses.

The present study will be the first to demonstrate that topical use of antiviral rinses could quantitatively reduce COVID-19 virus in the oro-naso-pharynx. Patients, physicians, nurses and dentists, all could be benefited with this findings of this study. Above all, if this is found to be effective, such gargles could be used as routine prophylaxis of patients visiting outpatient clinics where the status of COVID-19 is not known.

**FIGURE 1: FLOW DIAGRAM OF STUDY –PARTICIPANTS’ TIMELINE {13}**

[figure not shown]

### Annexure: 1 (Operational Definitions)

1. COVID-19: An RNA based virus, member of coronavirus family responsible for the current pandemic that has affected nearly 3.7 million cases worldwide. The symptoms are similar to the infection of caused by SARS (severe acute respiratory syndrome). We intend to induct PCR confirmed COVID-19 cases which are within 7 days on infection onset.
2. PCR: Polymerase chain reaction. It will be used to amplify genetic material required for testing. Both the baseline and endpoint specimens will be obtained from posterior pharyngeal wall by trained personnel using proper PPE.
3. Cytokine array: A multiplex ELISA method will be used to detect fluorescence antibody against predefined antigen. We will study the following cytokine profile IL-2, IL-4, IL-6, IL-10, TNF- $\alpha$ , IFN- $\gamma$  and IL-17 among COVID-19 patients in the present study.
4. Neem extract: Biological name *Azardirachta indica*. This has a number of active chemicals that have antiviral activity. A solution will be compounded at University Karachi, Chemistry department laboratory to be used as oral rinse and nasal lavage for COVID-19 patients.
5. PPE: This refers to Personal protective equipment including protective clothing, N-95 mask, eye wear and other garments or equipment designed to protect the person or infection.
6. Gargle: Transiently keeping some fluid in the oral cavity/ oro-pharynx followed by spitting off with an objective of physically rinsing off the mucosal membrane. We will use five different solutions as gargles.
7. Nasal lavage: Passing a fluid in the nose following by sneezing like action to mechanically clear the nasal cavity. The gargling solutions will employed in nasal lavage using a special syringe shown below.

[figure not shown]

Figure 2: Syringe to be used for nasal lavage
